**Introduction:**

Evidence-based treatments for major depressive disorder (MDD) possess moderate efficacy. However, applicability, availability and acceptability of these treatments are limited. Antidepressant treatment is not acceptable for a vast number of patients with MDD, resulting in high rates of non-compliance. Short-term psychotherapy is not effective in the majority of these patients and not routinely available. Moreover, It is estimated that at least 10-20% of all patients do not respond at all to these treatments even when applied simultaneously and in residential contexts. Therefore, new, acceptable, and efficacious treatments for MDD will help to fill the therapeutic gap that is left by current evidence-based treatments.

**Neurofeedback**

There is a growing interest in neurofeedback (NF) as a treatment for psychiatric disorders including MDD {Lofthouse, 2011 #4632}. It is thought that this technique, within an operant conditioning framework, helps individuals to regulate cortical elektroencephalographic (EEG) activity while receiving feedback from a visual or acoustic signal. The resulting change in EEG activity is presumed to be associated with a change in underlying cortical activation, and subsequently to result in a reduction of associated psychiatric symptoms {Evans, 1999 #2911}. NF is an outstanding example of a non-invasive brain-computer interface which may be particularly appealing to younger patients. Despite widespread claims of efficacy of NF in MDD, the scientific literature consists only of some case-reports and 1 case-control study.

Nevertheless, NF may be an efficacious treatment for MDD.

**Neurophysiology of depression**

Results from fundamental research indicate that MDD appears to be characterized by relatively more left than right resting (alpha, 8-13 Hz) activity in prefrontal regions {Stewart, 2011 #4491}, although some inconclusive studies exist (e.g., {Pizzagalli, 2002 #4526}. This finding has become known as alpha-asymmetry (AA) in MDD. AA is considered as a representation of reduced approach-related behaviours and reduced sensitivity to rewards in MDD {Stewart, 2010 #4493}.

**Neurofeedback als a treatment for MDD**

The intervention will consist of reducing AA in the prefrontal cortex with the use of NF. Participants will learn to increase elektrophysiological brain activity in the left prefrontal cortex in comparison to activity in their right prefrontal cortex. NF-sessions will take place in a maximum of 30 sessions three times each week. Every session will have a duration of 3x8 minutes separated by 4 minutes rest. Primary goal of the pilot-study is obtaining preliminary evidence about possible effectiviness of NF as a treatment for MDD. If at least 50% of the participants will respond (>50% reduction of symptomatology) at the end of treatment, this will considered as an indication of possible effectiveness. Further research in the context of a RCT will be carried out to establish efficacy.

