**Method**

*Design:*

10 Participants, meeting criteria for MMD according to DSM-IV-TR, will be recruited at the unit for treatment of mood disorders at the RIAGG Maastricht, and by advertisements in local media. Formal axis-1 diagnosis will be established with the SCID-1, a formal classification instrument for DSM-IV axis-1 disorders {First, 1995 #4782}. After signing informed consent, subjects will participate in the study.

*Inclusion criteria:*

- Primary axis-1 disorder of Major Depressive Disorder fulfilling DSM-IV criteria {APA, 1994 #87}.
- Written informed consent.

*Exclusion criteria:*

- History of brain trauma (commotio or constusio cerebri)
- Current use of antipsychotics, moodstabilizers or benzodiazepines. Current use of antidepressants is permitted if this medication is not changed within a period of 6 weeks prior to participation in the study. Additionally, no changes in antidepressant medication are allowed during active participation in the study.
- Chronic depression (> two years duration).
- Dysthymia as a primary axis-1 diagnosis
- Bipolar disorder as a primary axis-1 diagnosis
- Severe suicidality (HDRS item # 3 with a score >2) or severe depression symptomatology (HDRS score > 25).
- Pregnancy.
- Comorbid anxiety disorders and personality disorders are permitted.

*Outcome measures*

Main outcome measures are the Quick Inventory of Depressive Symptoms (QIDS-SR; {Rush, 2003 #2772}, the Hamilton Depression Rating Scale (HDRS; {Hamilton, 1967 #1598}, the Remission from Depression Questionnaire (RDQ; {Zimmerman, 2013 #5538} and change in AA between frontal cortical regions.

- The QIDS-SR is a 16-item self-rating scale to assess symptom severity of MDD and will be administered prior to each NF session (3 times a week).
- The HDRS is a 17-item clinician-rated scale for estimating severity of depression during the past week. It will be administered once a week by a trained research assistant during the 6-week study period.
- Before and after every NF session, participants will fill out the PANAS and the TEPS. The PANAS measures momentary positive and negative affects, the TEPS measures anhedonia. Goal of obtaining these instruments is to assess changes in emotions after each NF session.
- At baseline, demografic and medical information will be collected.

*Intervention:*

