After informed consent is obtained, the NF intervention will consist of maximum 30 sessions, each lasting 3 x 8 minutes divided by 2 breaks of 4 minutes. Prior to and after each session, baseline EEG alpha-activity will be measured at right- and left frontal regions. Sessions will be done 3 times a week. If after 30 sessions no improvement in clinical condition has occurred, we will offer participants an evidence-based treatment in our outpatient mental health center (RIAGG Maastricht) or the outpatient facility of the department of psychiatry at the Maastricht University Hospital. Additionally, the NF treatment will be stopped in cases of severe suicidality or severe depression symptomatology ( QIDS-SR score > 21). In these cases, the research assistant will contact the principal investigators who will responsible for referral for standard depression treatment.

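### Thirty sessions at three per week take 10 weeks, but the protocol sets the study at 6 weeks, which holds only 18 sessions

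*Protocol*

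**What the plan says.** The length of treatment is given in two ways.

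**By sessions.** In the Protocol, *Neurofeedback als a treatment for MDD*: "NF-sessions will take place in a maximum of 30 sessions three times each week". *Method, Intervention* repeats the maximum of 30 and the frequency ("Sessions will be done 3 times a week"). It then attaches a clinical decision to the end of that course: "If after 30 sessions no improvement in clinical condition has occurred, we will offer participants an evidence-based treatment".

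**By weeks.** *Method, Outcome measures* says of the HDRS: "It will be administered once a week by a trained research assistant during the 6-week study period". *Ethical issues* gives 6 weeks as the longest the study will last and uses that figure to argue that the burden on participants is limited.

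The pilot's success rule, in *Neurofeedback als a treatment for MDD*, is set at the end of treatment and names no scale: "If at least 50% of the participants will respond (>50% reduction of symptomatology) at the end of treatment". The HDRS and the QIDS-SR are both listed as main outcomes. The HDRS is the only instrument described as clinician-rated. The QIDS-SR is self-rated and "will be administered prior to each NF session (3 times a week", so it continues for as long as sessions do.

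**The concern.** At the stated frequency, the number of sessions and the number of weeks do not describe the same course of treatment, and nothing in the protocol reconciles them. Two things depend on which figure governs: whether the decision after session 30 can ever be taken, and whether the HDRS is available when response is judged. A research assistant who follows the Outcome measures text literally would stop HDRS ratings at week 6, even for a participant still in treatment. With 10 participants, each response status moves the response rate by 1/10 = 10 percentage points, so the scale and time point behind each status need to be clear.

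**Working it through.** **Inputs**

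- Maximum sessions: 30 (*Neurofeedback als a treatment for MDD*; *Method, Intervention*).
- Frequency: 3 per week (same two places).
- Duration: 6 weeks (*Method, Outcome measures*, for the HDRS; *Ethical issues*, for the study).
- Participants: 10 (*Method, Design*).

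**Step 1. Try to reproduce the stated 6 weeks**

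Weeks = maximum sessions / sessions per week = 30/3 = 10. The stated 6 weeks is not reproduced.

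**Step 2. Sessions that fit into the stated duration**

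Sessions = weeks × sessions per week = 6 × 3 = 18, which is 18/30 = 60% of the maximum.

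**Step 3. Frequency that would reconcile the two figures**

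30/6 = 5 sessions per week. The protocol states this nowhere.

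**Step 4. Consequence under each reading**

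- *Six weeks governs.* Treatment ends by about session 18 and weekly HDRS covers all of it. The decision after session 30 can never be reached.
- *Thirty sessions governs, and the HDRS text is followed literally.* The last planned HDRS falls around session 18. What lies beyond it depends on how long the participant continues:

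| Sessions received | Weeks at 3 per week | Weeks after week 6 | Sessions after session 18 | Share of course |
|---|---|---|---|---|
| 18 or fewer | up to 6 | 0 | 0 | 0% |
| 24 (illustration) | 24/3 = 8 | 8 − 6 = 2 | 24 − 18 = 6 | 6/24 = 25% |
| 30 (maximum) | 30/3 = 10 | 10 − 6 = 4 | 30 − 18 = 12 | 12/30 = 40% |

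The percentages are shares of the session course. They are not effects on any result.

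**Step 5. What remains measured after week 6**

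The QIDS-SR (before each session), frontal alpha activity (before and after each session), and the PANAS and TEPS (before and after each session) are tied to sessions and continue with them. No schedule is given for the RDQ, so nothing is concluded about it.

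**The case against.** The arithmetic is not in dispute. The case against concerns what follows from it.

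- **The HDRS gap needs a mixed reading.** It appears only if treatment runs past week 6 while the 6-week wording still binds the HDRS. If 6 weeks binds everything, there is no gap. If the 6 weeks is a carry-over, the HDRS text may simply mean weekly throughout the study. A carry-over is plausible, because *Procedure* and *Ethical issues* mention an active arm, sham treatment and a previous pilot. This objection stands, and the gap is stated here only as conditional. It does not remove the conflict: the 6 weeks is current text, and it also appears in the protocol's own outcome section.
- **Both figures are maxima.** A reader might infer that the schedule cannot be carried out at all. That is too strong, since a course of up to 18 sessions within 6 weeks breaches neither limit. What cannot occur in 6 weeks at 3 per week is session 30 and the decision attached to it.
- **Response can still be scored.** A reader might infer that the success rule fails, or that the response rate is biased. The documents do not support this. The rule names no scale, the QIDS-SR runs to just before the last session, and the number of participants who will pass session 18 is not given.
- **Safety monitoring continues.** A reader might infer that no severity check remains after week 6. The numerical threshold for stopping treatment is a QIDS-SR score above 21, and the QIDS-SR is taken before every session.

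**Conclusion.** The point holds as an internal inconsistency. Up to 30 sessions at 3 per week means 10 weeks, the stated duration is 6 weeks (18 sessions), and one of the figures has to change. The difference is 4 weeks and 12 sessions.

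One of two consequences follows. Either the decision after session 30 is unreachable, or participants who continue past session 18 have no planned HDRS for up to the last 4 weeks. In the second case response at the end of treatment could not be read on the HDRS. That consequence assumes that treatment runs past week 6, that the HDRS text is followed literally, and that the end of treatment is each participant's last session. Participants with 18 or fewer sessions are not affected. No effect on the response rate is claimed. This should be corrected, but it does not invalidate the pilot.

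**What to change.** In *Method, Outcome measures*, schedule the HDRS weekly until the end of treatment, including a rating at the end of treatment. Then make the durations agree in one of two ways. The choice is the sponsor's.

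**Keep 30 sessions.** State up to 10 weeks in *Method, Outcome measures* and in *Ethical issues*, and revise the burden justification there, because that argument and its comparison with antidepressant trials rest on 6 weeks. The cost is 4 extra HDRS ratings (weeks 7–10), plus 1 if the end rating is separate. That is at most 4–5 per participant, or 40–50 for 10 participants, by the existing research assistant. The waiting-list argument survives: 70 days / 30.4 = 2.3 months, against a wait of 3–4 months.

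**Keep 6 weeks.** State a maximum of 18 sessions in *Neurofeedback als a treatment for MDD* and *Method, Intervention*, and move the decision point from session 30 to session 18. The cost is 0–1 extra HDRS rating per participant (0–10 in total). The maximum course also becomes 12 sessions (40%) shorter, which changes the intervention.

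The restriction on antidepressant changes is not an added cost of either option. It already applies to the whole of active participation: "no changes in antidepressant medication are allowed during active participation in the study".

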**Hypothesis**

In this study, we have the following research objective:

1. NF aimed at reduction of AA is associated with a reduction in depressive symptomatology.

**Method**

*Design:*

10 Participants, meeting criteria for MMD according to DSM-IV-TR, will be recruited at the unit for treatment of mood disorders at the RIAGG Maastricht, and by advertisements in local media. Formal axis-1 diagnosis will be established with the SCID-1, a formal classification instrument for DSM-IV axis-1 disorders {First, 1995 #4782}. After signing informed consent, subjects will participate in the study.

*Inclusion criteria:*

- Primary axis-1 disorder of Major Depressive Disorder fulfilling DSM-IV criteria {APA, 1994 #87}.
- Written informed consent.

*Exclusion criteria:*

- History of brain trauma (commotio or constusio cerebri)
- Current use of antipsychotics, moodstabilizers or benzodiazepines. Current use of antidepressants is permitted if this medication is not changed within a period of 6 weeks prior to participation in the study. Additionally, no changes in antidepressant medication are allowed during active participation in the study.
- Chronic depression (> two years duration).
- Dysthymia as a primary axis-1 diagnosis
- Bipolar disorder as a primary axis-1 diagnosis
- Severe suicidality (HDRS item # 3 with a score >2) or severe depression symptomatology (HDRS score > 25).
- Pregnancy.
- Comorbid anxiety disorders and personality disorders are permitted.

*Outcome measures*

Main outcome measures are the Quick Inventory of Depressive Symptoms (QIDS-SR; {Rush, 2003 #2772}, the Hamilton Depression Rating Scale (HDRS; {Hamilton, 1967 #1598}, the Remission from Depression Questionnaire (RDQ; {Zimmerman, 2013 #5538} and change in AA between frontal cortical regions.

- The QIDS-SR is a 16-item self-rating scale to assess symptom severity of MDD and will be administered prior to each NF session (3 times a week).
- The HDRS is a 17-item clinician-rated scale for estimating severity of depression during the past week. It will be administered once a week by a trained research assistant during the 6-week study period.
- Before and after every NF session, participants will fill out the PANAS and the TEPS. The PANAS measures momentary positive and negative affects, the TEPS measures anhedonia. Goal of obtaining these instruments is to assess changes in emotions after each NF session.
- At baseline, demografic and medical information will be collected.

*Intervention:*

After informed consent is obtained, the NF intervention will consist of maximum 30 sessions, each lasting 3 x 8 minutes divided by 2 breaks of 4 minutes. Prior to and after each session, baseline EEG alpha-activity will be measured at right- and left frontal regions. Sessions will be done 3 times a week. If after 30 sessions no improvement in clinical condition has occurred, we will offer participants an evidence-based treatment in our outpatient mental health center (RIAGG Maastricht) or the outpatient facility of the department of psychiatry at the Maastricht University Hospital. Additionally, the NF treatment will be stopped in cases of severe suicidality or severe depression symptomatology ( QIDS-SR score > 21). In these cases, the research assistant will contact the principal investigators who will responsible for referral for standard depression treatment.

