At the start of each NF session, the baseline EEG is being measures without NF to assess baseline AA which serves as a starting point for feedback. Measuring baseline prior to each session is necessary as can be expected that, at least in the active arm, AA decreases over time. Data collection will be channeled through an acquisition PC with a BrainAmp DC EEG amplifier (Brain Products) using a 1000 Hz sample frequency. Online calculations are done by a filter written for BrainVision RecView. The data will be epoched online into 2.048-s epochs that overlap by 75% and then transformed by a fast Fourier transform (FFT) to the frequency domain (frequency resolution 0.488 Hz). Every 0.512 second, the power within the alpha frequency band (7.8 Hz – 13.1 Hz) of both F3 and F4 will be calculated. AA is computed as the difference of the natural log-transformed F3 and F4-alpha power: Ln(F3-alpha) – Ln(F4-Alpha). Current asymmetry is subsequently compared to the personal mean baseline asymmetry. The result of the calculation will be sent to a stimulus PC running Presentation stimulus delivery software (Neurobehavioral Systems) with an 8-bit parallel port (LPT-port) to control a paradigm showing a visual representation of the asymmetry. In the Presentation paradigm, the last 20 values of the asymmetry are used in a moving average to prevent ‘jitter’ in the feedback. Participants receive feedback with visual feedback; they are instructed to increase the level of a thermometer that is shown on a flatscreen. Additionally, a numerical score below the thermometer indicates their actual total performance. This score is adjusted (i.e. increased) continuously by a number ranging from 0 and 128, depending on the level of the thermometer. In this way a good actual performance (a shift in asymmetry in the desired direction) results in an increasing total score. A big shift in the desired direction results in a rapidly increasing total score, whereas a small shift in the desired direction results in a slow increasing total score. A shift in the undesired direction produced no change in total score. The purpose of this total performance score is to give participants feedback on the differential effect of the sessions.

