# **Ethical issues**

Participants will be receive written and verbal information about the procedure and have the right to discontinue participation at any moment. Partcipants wil receive either an experimental or sham experimental treatment for their depressive disorder. To minimize burden resulting from participation in the study, the duration of the study is kept to a maximum of 6 weeks. This duration is based on data from our pilot-study and is totally comparable to the duration of RCT’s that examine novel antidepressants with the use of placebo. Given the extensive waiting-lists for regular evidence-based treatments for depression (3-4 months), participation in the study does not lead to additional delay in the start of standard therapy. Thus, those participants that wish to receive standard antidepressant treatment after participation in the study, will receive such treatment within a normal time-frame.

As mentioned earlier, no side-effects of NF are reported in the literature. Moreover, in our pilot-study in depressed participants, we did not observe any side-effects.

There will be an independent physician available to address all questions and concerns of potential participants. All participants will provide written informed consent. Their data will be collected in a anonymized in a central database in our laboratory. Participants can withdraw consent at any moment without any restrictions. If requested, all participants can be informed of the final results after completion of the study.

All data will be coded and stored anonymously. Each participant will be assigned to an unique code. Access to data and code are restricted to research assistants and principal investigators. The code that entails information about active or sham-treatment will be opened after completion of the study.

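### The medication criteria look only at current use, so a person who has just stopped a psychotropic drug can enter a pilot judged without a comparator

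*Protocol*

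**What the plan says.** One bullet of the exclusion criteria (Protocol, Method) covers all medication.

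- **Antipsychotics, mood stabilisers, benzodiazepines.** The criterion is "Current use of antipsychotics, moodstabilizers or benzodiazepines". No period before entry is attached, and no other section adds one.
- **Antidepressants, before entry.** "Current use of antidepressants is permitted if this medication is not changed within a period of 6 weeks prior to participation in the study".
- **Antidepressants, on study.** "Additionally, no changes in antidepressant medication are allowed during active participation in the study".

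Three other statements bear on the point. The exclusion of "severe depression symptomatology (HDRS score > 25") caps the entry score on the Hamilton scale (HDRS) at 25. The Method section also states: "At baseline, demografic and medical information will be collected". The success criterion, in the section on neurofeedback as a treatment for MDD, is "If at least 50% of the participants will respond (>50% reduction of symptomatology) at the end of treatment"; meeting it counts as a sign of possible effectiveness, with efficacy left to a later randomised trial.

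**The concern.** The investigators accept that a recent drug change can disturb the outcome, since they ask for 6 weeks of stable antidepressant treatment. No rule reaches the person who has recently stopped a drug, in any of the four classes.

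Such a person's symptoms may move for reasons unrelated to neurofeedback. If the entry score includes discontinuation symptoms that later fade, the fall looks larger than it is. If a helpful drug was stopped and its loss shows only after entry, a real response may be hidden. The success rule compares each participant only with his or her own baseline, so it cannot separate either effect from the intervention. An analysis plan could not repair this afterwards, because it cannot restore a drug-free interval that was not required at entry.

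**Working it through.** **1. Who each rule reaches**

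| Situation at entry | Three excluded classes | Antidepressants |
|---|---|---|
| Taking the drug, dose stable for 6 weeks | Excluded | Eligible |
| Taking the drug, dose changed within 6 weeks | Excluded | Not eligible |
| Stopped the day before | Eligible: not current use | Not clearly reached: the rule conditions permitted current use |
| Stopped long ago | Eligible | Eligible |

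The third row is the gap, and it is the same for all four classes.

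**2. Weight of one participant**

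Inputs: 10 participants (Method) and a bar of at least 50% responders. The bar is 0.50 × 10 = 5. One participant is 1/10 = 10 percentage points.

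**3. How easily one person could be misclassified (illustration)**

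The Protocol states no figure for this. Assumptions: the HDRS is the response scale (the success rule names none); the entry score is 25, the highest allowed; d points are drug-related, with d = 2, 4 or 6. E is the end score.

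*False response:* d points of the entry score fade completely. This needs 1 − E/25 > 0.5 and 1 − E/(25 − d) ≤ 0.5, that is (25 − d)/2 ≤ E < 12.5.

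| d | End scores affected | Observed fall | Fall without the drug-related points |
|---|---|---|---|
| 2 | 12 | 52.0% | 47.8% |
| 4 | 11, 12 | 56.0%, 52.0% | 47.6%, 42.9% |
| 6 | 10, 11, 12 | 60.0%, 56.0%, 52.0% | 47.4%, 42.1%, 36.8% |

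Entry scores of 22, 20 and 18 also give 1, 2 and 3 end scores.

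*Hidden response:* d points of worsening appear after entry and are still present at the end. This needs 1 − E/25 ≤ 0.5 and 1 − (E − d)/25 > 0.5, that is 12.5 ≤ E < 12.5 + d. The affected end scores are 13–14 for d = 2, 13–16 for d = 4 and 13–18 for d = 6.

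**4. Effect on the decision if one person is misclassified (illustration)**

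Assume the other participants respond independently with probability p apart from any neurofeedback effect. The Protocol gives no p. With no drug effect the chance of success is P(X ≥ 5), X ~ Bin(10, p). If one participant is certain to count as a responder it is P(X ≥ 4), X ~ Bin(9, p). If one is certain to count as a non-responder it is P(X ≥ 5), X ~ Bin(9, p).

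| Assumed p | No drug effect | One certain responder | One certain non-responder |
|---|---|---|---|
| 20% | 0.033 | 0.086 | 0.020 |
| 30% | 0.150 | 0.270 | 0.099 |
| 40% | 0.367 | 0.517 | 0.267 |

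These figures show leverage, not expected bias. Treating the affected person's result as certain puts them at the upper end of what one participant could do.

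**The case against.** Four points can be made on the other side.

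- **The consequence is not shown.** This stands. The Protocol gives no frequency of recent discontinuation, no size of effect and no direction. The score windows and probabilities above rest on assumptions.
- **The root problem is the missing comparator.** This stands in part. The rule is equally open to spontaneous improvement and expectancy, which a drug-free interval would not remove. But recent discontinuation is one source that an entry criterion can remove. The references to a control do not change this: Procedure says "at least in the active arm, AA decreases over time" and Ethical issues says "Partcipants wil receive either an experimental or sham experimental treatment for their depressive disorder", yet Method describes one group of 10 and the success rule uses no control.
- **The three classes are not handled more laxly than antidepressants.** A reader might infer from the 6-week sentence that recent antidepressant stoppers are kept out while recent benzodiazepine stoppers are let in. The wording does not support that contrast. It is a stability condition on people who take an antidepressant, so a person who has stopped one is not clearly reached either. The gap is therefore common to all four classes.
- **Nothing is wrong with the on-study rules.** A reader might also infer, because the on-study sentence names only antidepressants, that participants are free to start one of the excluded drugs after entry. The text does not establish this. An exclusion naturally reads as continuing, and an excluded class has no dose to hold constant, so a missing parallel sentence is weak evidence of a gap. Saying so expressly would be a clarification only.

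**Conclusion.** The point holds as a gap in the entry criteria: no interval off drug is required for antipsychotics, mood stabilisers or benzodiazepines, and the antidepressant rule does not clearly cover stopping. With an uncontrolled before–after criterion, symptoms that follow a recent discontinuation could be credited to neurofeedback or held against it.

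The severity is minor. That one participant carries 10 percentage points against a bar of 5 of 10 follows from the Protocol; everything beyond that is assumed. On those assumptions a false response needs an end score in a window of one to three points. The decision at stake is also small, since meeting the bar only supports going on to a randomised trial. This is a cheap improvement, not a flaw that undermines the pilot.

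**What to change.** In the exclusion criteria (Protocol, Method):

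1. Exclude use of antipsychotics, mood stabilisers or benzodiazepines at entry or within the 6 weeks before participation. Six weeks is the window the Protocol already uses for antidepressants.
2. Reword the antidepressant rule so that starting, stopping or changing the dose of an antidepressant within those 6 weeks all count as a change.

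Optionally, state that the three classes remain excluded during active participation, with clinical need left to the treating clinician.

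The cost is two wording changes and a medication-history question at baseline, where medical information is already collected. A few recent discontinuers would enter later or not at all, which slows recruitment slightly.

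### Psychotherapy is neither required to be stable at entry nor recorded during the study, so improvement from it could count as neurofeedback response

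*Protocol*

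**What the plan says.** **Concurrent treatment (Method, Exclusion criteria).** Antipsychotics, mood stabilizers and benzodiazepines are excluded. For antidepressants the entry rule is "Current use of antidepressants is permitted if this medication is not changed within a period of 6 weeks prior to participation in the study", and the conduct rule is "Additionally, no changes in antidepressant medication are allowed during active participation in the study". Every restriction on concurrent treatment concerns a drug.

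**Psychotherapy.** It is named only in the Introduction, as one of the existing treatments for depression. No entry criterion, conduct rule or scheduled assessment mentions it. Demographic and medical information is collected at baseline only (Method, Outcome measures).

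**Sample and source (Method, Design).** The sample is "10 Participants, meeting criteria for MMD according to DSM-IV-TR". Participants "will be recruited at the unit for treatment of mood disorders at the RIAGG Maastricht, and by advertisements in local media".

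**Success rule (Neurofeedback als a treatment for MDD).** The rule reads "If at least 50% of the participants will respond (>50% reduction of symptomatology) at the end of treatment", and then "this will considered as an indication of possible effectiveness". It names no comparison group and makes no allowance for other treatment.

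**Timing of standard care.** Ethical issues puts the wait for regular treatment at 3-4 months and expects those who want standard treatment to receive it after the study. Method, Intervention offers evidence-based treatment to participants who have not improved after 30 sessions.

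**The concern.** The antidepressant rule shows that the authors saw the problem: if other treatment changes around the time of neurofeedback, a fall in symptoms cannot be attributed to neurofeedback. The same reasoning applies to psychotherapy, but the rule stops at drugs.

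Two kinds of participant are affected. One began psychotherapy shortly before entry, which is plausible for patients recruited at a treatment unit. The other had already waited some time for standard therapy and starts it during the neurofeedback weeks. Followed as written, the plan admits the first, keeps the second, and counts either as a responder if symptoms fall by more than half. Because the rule compares with nothing, the final count cannot separate the two sources of improvement. A later analysis plan could not repair this, since it cannot restore stability at entry or use information that was never collected.

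What is at stake is the pilot's primary conclusion: whether the responder rate indicates possible effectiveness of neurofeedback.

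**Working it through.** **The plan's own figure.** The protocol gives no alpha, power, sample-size derivation or null response rate. Its only figure is the threshold: 50% × 10 = 5 responders. Each responder moves the rate by 1/10, or 10 percentage points.

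**Can therapy overlap with neurofeedback?**
- Maximum course: 30 sessions ÷ 3 per week = 10 weeks.
- Stated wait: 3-4 months, about 13 to 17 weeks.
- Someone who joins the list on the day of entry would usually not reach therapy during the course.
- Someone who has already waited more than 13 − 10 = 3 weeks (for a 3-month list) or 17 − 10 = 7 weeks (for a 4-month list) could.
- Outcome measures and Ethical issues give a 6-week study instead. On that figure the thresholds are 13 − 6 = 7 and 17 − 6 = 11 weeks. The two durations disagree and need reconciling, but overlap is possible under either.
- Therapy already under way at entry is not touched by the waiting list at all.

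**How much could it move the rule?** The documents give none of the response rates, so the following are assumptions:
- neurofeedback has no effect;
- participants without other therapy respond with probability b = 0.20 or 0.30;
- k of the 10 are in concurrent psychotherapy and respond with probability q = 0.40 or 0.50.

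With no one in therapy, P(X ≥ 5) = Σ C(10, x) bˣ (1 − b)¹⁰⁻ˣ for x = 5 to 10. This gives 3.3% at b = 0.20 and 15.0% at b = 0.30.

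With k in therapy, X = A + B, where A is binomial (k, q) and B is binomial (10 − k, b). For k = 1 and q = 0.40 this is P(B ≥ 5) + 0.40 × P(B = 4), with B binomial (9, b):
- b = 0.20: 0.0196 + 0.40 × 0.0661 = 0.0460
- b = 0.30: 0.0988 + 0.40 × 0.1715 = 0.1674

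The other cells are the same sum done exactly:

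| In therapy (k of 10) | Response in therapy (q) | P(rule met), b = 0.20 | P(rule met), b = 0.30 |
|---|---|---|---|
| 0 | – | 3.3% | 15.0% |
| 1 | 0.40 | 4.6% | 16.7% |
| 2 | 0.40 | 6.3% | 18.6% |
| 3 | 0.40 | 8.5% | 20.5% |
| 3 | 0.50 | 12.2% | 26.7% |
| 5 | 0.40 | 14.4% | 24.7% |
| 5 | 0.50 | 23.8% | 36.5% |

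The increase runs from under 2 percentage points (one participant, modest therapy effect) to about 21 (five participants, larger effect). At b = 0.30, the 15.0% in the first row owes nothing to psychotherapy; it comes from a rule without a comparison.

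**The case against.** **Standard care is placed after neurofeedback.** Ethical issues cites the waiting list to argue that participation delays nothing. Intervention offers other treatment after 30 sessions without improvement, or by referral once neurofeedback has been stopped. The Introduction adds that psychotherapy is not routinely available. This stands as a reason to expect limited overlap. It describes timing, however, and forbids nothing, and it does not reach therapy already under way. A reader might infer that therapy gains will in fact enter the count; the documents support only that they could.

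**The number exposed is unknown.** Recruitment is also by advertisement, and no split between sources is given. The Introduction says short-term psychotherapy does not work in most of these patients, so a 50% response is at the upper edge of what the document supports. That stands, and is why the table includes one or two participants at 40%.

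**It is a pilot followed by a controlled trial.** A reader might infer that this rule is the go signal for that trial. The text does not say so: it calls a 50% response an indication of possible effectiveness and states, without a condition, that an RCT will be carried out. The bias concerns how the pilot result is read, not a stated decision gate.

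**There may be a sham group.** A reader might take the design to be plainly uncontrolled. Procedure mentions an active arm, and Ethical issues mentions sham treatment and a code opened at completion. These do not fit the 10-participant design, in which no second group is described. Whichever is right, the success rule itself makes no comparison.

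**Scoring could sit in an analysis plan.** In part, yes. Entry criteria and what is asked at visits belong in the protocol.

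**Conclusion.** The point holds in a limited form. The protocol keeps drug treatment constant, leaves psychotherapy without a stability requirement at entry or a record during the study, and judges success by a responder count with no comparison. Where psychotherapy helps, the bias in that count is upward.

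Its size cannot be determined from the documents. Under the assumptions above (no neurofeedback effect, base response of 20-30%, one to five of ten in therapy responding at 40-50%), the chance of meeting the rule rises from 3.3% to between 4.6% and 23.8%, or from 15.0% to between 16.7% and 36.5%. If nobody is in therapy, there is no bias from this source. The gap should be closed because closing it is cheap and the data cannot be recovered afterwards, not because a large bias has been shown.

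**What to change.** 1. **Entry.** Extend the stability principle already used for antidepressants to psychotherapy directed at depression, with the sponsor setting the window.
2. **Recording.** Ask about any other depression treatment at baseline and at each weekly HDRS assessment, with start date and any change.
3. **No bar on care.** Do not prevent participants from taking up standard treatment. A bar would sit badly with the assurance in Ethical issues that participation adds no delay.
4. **Scoring for the 50% rule.** Keep anyone who starts or changes other depression treatment in the denominator of 10 and count that person as a non-responder. Report alongside it the count using that person's observed response, so that the effect of the choice is visible.
5. **Design text.** Reconcile the references to an active arm (Procedure) and sham treatment (Ethical issues) with the 10-participant design, since that determines whether any comparison exists.

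**Cost.** One eligibility sentence, one question at visits that already take place, and one line in the success rule. A few candidates in recently started therapy would have to wait or would be ineligible, and the responder rate may come out slightly lower.
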